## Abstract

The COVID-19 pandemic has amplified mental health problems and highlighted inequitable gaps in care worldwide. In response there has been an explosion of digital interventions such as smartphone applications (“apps”) to extend care. The objective of this trial is to evaluate the effectiveness and cost-effectiveness of a digital depression intervention (*VMood*), delivered via a smartphone app. VMood is adapted from an in-person intervention that was delivered by non-specialist providers and shown to be effective in the Vietnamese context in our previous trial (2016–2019). A stepped-wedge, randomized controlled trial will be conducted across eight provinces in Vietnam. Adults aged 18 years and over will be recruited through community-based primary care centres and screened for depression using the embedded Patient Health Questionnaire-9 (primary outcome measure). Participants scoring 10–19, indicating depression caseness, will be randomly allocated to the intervention or control group until the target of 336 is reached. Secondary outcome measures will examine the effect of the intervention on commonly co-occuring anxiety, quality of life and work productivity, along with use of alcohol and tobacco products. Assessments will be administered through an online survey platform (REDCap) at baseline, and at every 3 months until 3 months post-intervention. Intervention-group participants will receive VMood for a 3-month period, with online support provided by social workers. Control-group participants will receive a limited version of the app until they cross into the intervention group. Generalized Linear Mixed-effect Models for clustered measures will be used for all outcomes data. We will conduct a cost-effectiveness analysis alongside the trial to capture VMood’s costs and benefits. This trial will provide evidence on the effectiveness and cost-effectiveness of a digital mental health intervention adapted from an in-person intervention. This trial will also contribute important information to the growing and promising field of digital mental health.

**Trail regulation.** Registered at ClinicalTrials.gov, identifier [NCT05783531].

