### Overall study design

The study will use a cluster stepped-wedge randomized controlled trial (RCT) design, with three stepped-wedges. Cluster stepped-wedge designs are pragmatic and appropriate for balancing scientific rigour with real world conditions, including the logistic and time constraints often faced by policy makers and health systems [29]. Stepped-wedge designs also represent an ethical approach in circumstances where access to evidence-based interventions is limited because they allow all participants to access the intervention as all clusters cross from the control into the intervention group [29].

In this study, randomization will occur at the commune level and communes will be assigned to receive either the VMood intervention or the control condition first. Participants in communes assigned to the control condition will be provided access to the VMood app and screening and assessment measures, but content will be limited to a video presenting general information about depression. In a typical stepped-wedge design, when a cluster crosses over from control to intervention, they remain in the intervention arm until the study is complete. In this case the intervention period will last three months in accordance with the VMood protocol. We will also collect follow-up data from each cluster three months after they have completed the intervention. Table 1 illustrates the timing of the intervention and control groups in the stepped-wedge design for one study district. Due to the size of the study, which will include 8 districts and 48 communes in total, all communes in the same district will begin the study at the same time but the entry of provinces will be staggered. The study has not started recruiting participants.

**Table 1 pone.0290328.t001:** VMood stepped wedge design by month—one district.

		1	2	3	4	5	6	7	8	9	10	11	12									
C1																						
C2																						
C3																						
C4																						
C5																						
C6																						
		Baseline																				
		Intervention																				
		Control																				
		Follow-up																				
	C	Commune																				

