### Participants

#### Setting

The study will be carried out in eight Vietnamese provinces that represent diversity in terms of population composition, economic status and availability of mental health service resources. The study will take place in one district of each province, including six communes (municipal subdivisions) in each district for a total of 48 communes [see Table 2]. For logistical reasons, selected provinces represent a mix of provinces that previously participated in the in-person RCT and those that have not, though different districts and communes will be selected in all provinces that participated in the previous study to avoid bias.

**Table 2 pone.0290328.t002:** Participating provinces, districts, and communes.

Province	District	Communes
1	1	1, 2, 3, 4, 5, 6
2	2	1, 2, 3, 4, 5, 6
3	3	1, 2, 3, 4, 5, 6
4	4	1, 2, 3, 4, 5, 6
5	5	1, 2, 3, 4, 5, 6
6	6	1, 2, 3, 4, 5, 6
7	7	1, 2, 3, 4, 5, 6
8	8	1, 2, 3, 4, 5, 6

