#### Inclusion and exclusion criteria

The trial will be implemented so that participants enter the study in a naturalistic manner. Community meetings will be organized to promote VMood, and all commune members will be invited to download the app, complete registration and informed consent and then complete the nine-item depression screening measure (Patient Health Questionnaire; PHQ-9 [30]). Healthcare staff members, funded by MOH, at the commune health stations and outpatient clinics will assist with publicizing the VMood app and encourage commune members to download it. Healthcare workers will be provided with information about the intervention as well as about the informed consent required to participate.

Inclusion criteria for the study are: 1) participant meeting depression caseness criteria based on the PHQ-9 measure (PHQ-9 score between 10–19) and 2) informed consent to participate in the study and complete all outcomes measures. Exclusion criteria include participants experiencing severe mental illness (PHQ-9 ≥ 20), including severe depression, suicidal ideation, or symptoms of other serious mental health conditions, who will be referred via an in-app notification to psychiatric and/or emergency care.

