### Sample size and power calculation

The power calculation assumes that each commune would recruit an average of 8 participants and retain 7 participants after attrition and that the proportion of depression caseness (defined as PHQ-9 score between 10–19) in the control group is 42%, the same as in the previous study [25]. The calculation shows that for a type I error rate of 0.05, and an intracluster correlation coefficient (ICC) of 0.01 (based on data from the previous study on the binary outcome of having depression), a total of 336 participants recruited from 48 clusters (i.e., communes) have at least 80% power to detect treatment differences when the proportion of depression caseness in the intervention group is ≤ 30% (Table 4 below) [46]. The power calculation was performed using Stata 17 [46].

**Table 4 pone.0290328.t004:** Power analysis.

Proportion of depression caseness in Intervention Condition	Power
0.30	81%
0.31	74%
0.32	66%
0.33	57%
0.34	48%

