### Randomization and blinding

Randomization will be done using permuted blocks (to conceal allocation) and will be stratified by district. The randomization sequence will be developed and controlled by an individual not otherwise involved in the study to ensure fidelity and supervised by co-author HX. After baseline assessment, communes will be randomly assigned to the three sequences (Table 1) in a 1:1:1 allocation ratio stratified by district in variable block sizes implemented in SAS v9.4 to prevent anticipated allocation of the communes to the treatment sequences.

Full blinding of participants will not be possible due to the nature of the intervention.

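### The abstract's rule of allocating participants until 336 is reached contradicts commune randomisation and the planned 8 recruits in each of 48 communes (384 enrolled, 336 retained)

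*Protocol article*

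**What the plan says.** The abstract of the protocol article gives the enrolment and allocation rule in one sentence: people scoring in the eligible PHQ-9 range "will be randomly allocated to the intervention or control group until the target of 336 is reached".

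The body gives a different rule:

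- **Unit.** Under Overall study design, "randomization will occur at the commune level and communes will be assigned to receive either the VMood intervention or the control condition first".
- **Timing, arms and strata.** Under Randomization and blinding, "After baseline assessment, communes will be randomly assigned to the three sequences (Table 1) in a 1:1:1 allocation ratio stratified by district".
- **Clusters.** Under Setting, one district in each of eight provinces, "including six communes (municipal subdivisions) in each district for a total of 48 communes".
- **Calendar.** Under Overall study design, "all communes in the same district will begin the study at the same time but the entry of provinces will be staggered".
- **Numbers.** Under Sample size and power calculation, "each commune would recruit an average of 8 participants" and would keep 7 after attrition. The same section then gives 336 as the total from 48 clusters and describes those 336 as recruited.

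On how people come forward, Inclusion and exclusion criteria says: "The trial will be implemented so that participants enter the study in a naturalistic manner".

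**The concern.** The abstract and the body differ on three things that define the trial: the unit that is randomised (person or commune), the number of allocation groups (two or three sequences), and what ends recruitment (a trial-wide count or a planned number per commune).

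The third difference matters in practice. In the sample size section, 336 can only be the number left after attrition, yet the abstract uses it as the point at which enrolment ends, and the sample size section itself attaches the word for enrolment to it. A team that closed recruitment at 336 enrolled would have fewer participants for analysis than the power table assumes. Since provinces start one after another, the last to start would be the most exposed to an early close. The Discussion relies on the spread of provinces for generalisability.

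**Working it through.** **Inputs.** From Sample size and power calculation: 8 recruited and 7 retained per commune, 48 communes, caseness 0.42 in control and 0.30 in intervention, type I error 0.05, ICC 0.01, Table 4. From Overall study design and Randomization and blinding: three sequences, 1:1:1. From Setting: 8 districts of 6 communes. Assumed, because not stated: two-sided test, four periods, 7 people per commune per period, no within-person correlation, binomial variance taken at the control rate.

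**1. What 336 is.**
- Recruited: 48 × 8 = 384.
- Retained: 48 × 7 = 336.
- Planned attrition: 1 − 7/8 = 12.5%, and 336 / (7/8) = 384.

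**2. Reproducing Table 4.** Hussey-Hughes variance for a stepped wedge with I communes and T periods:

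Var = I·s²·(s² + T·t²) / [(I·U − W)·s² + (U² + I·T·U − T·W − I·V)·t²]

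Here s² is the residual variance divided by the number per commune-period and t² is the between-commune variance. U is the number of treated commune-periods. W is the sum over periods of the squared number of treated communes. V is the sum over communes of the squared number of treated periods.

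- 16 communes per sequence, treated for 3, 2 and 1 of the 4 periods: U = 16 × 6 = 96; W = 16² + 32² + 48² = 3584; V = 16 × (9 + 4 + 1) = 224.
- s² = 0.42 × 0.58 / 7 = 0.0348; t² = (0.01/0.99) × 0.2436 = 0.00246.
- Var = 48 × 0.0348 × (0.0348 + 4 × 0.00246) / (1024 × 0.0348 + 2560 × 0.00246) = 0.00178, so SE = 0.0422.
- Power = Φ(0.12/0.0422 − 1.96) = **81.2%**.

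The other rows give 74.2, 66.0, 56.9 and 47.5%, against the stated 74, 66, 57 and 48%. Table 4 is therefore matched by a commune-level stepped wedge with 7 retained in each of 48 communes. Individual 1:1 allocation of 168 per arm gives 63.1% and would need 250 per arm for 80%.

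**3. If 336 is where enrolment stops.** Retained: 336 × 7/8 = 294.

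| Where the 294 are | Communes × retained | SE | Power at 0.30 |
|---|---|---|---|
| Spread over all communes | 48 × 6.125 | 0.0449 | 76.2% |
| First seven districts only | 42 × 7 | 0.0451 | 75.9% |

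With the average of the two arms' variances, (0.2436 + 0.21)/2 = 0.2268, full-plan power is 83.9% and the 42-commune case gives 78.8%. The loss is about 5 points under either variance. It comes almost entirely from counting 336 as enrolled; which communes supply the people hardly matters for power.

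**4. When the stop would be reached.** 336/8 = 42 communes = 7 districts of 6. With the matching recruited total, 384/8 = 48 communes, and with 7 per commune, 336/7 = 48. The missing district therefore arises from setting a retained total against a recruited rate, and only if districts fill one after another.

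**The case against.** The strongest reply is that this is one condensed abstract sentence. The body is consistently commune-level: the design section, the randomisation section, the commune random effects in the analysis model and the power table all agree. The abstract itself calls the trial stepped-wedge, with crossing over and clustered measures. This stands. A reader might infer from the abstract that enrolment actually runs by individual allocation, and the documents do not support that.

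A reader might also infer that the last province will be shut out. No body section sets a first-come stop across provinces. All 48 communes are listed, the 336 are said to come from 48 clusters, and recruitment is planned as an average per commune. The loss needs the abstract's stop applied literally, communes averaging more than 7, and nearly sequential entry; the text says only that entry is staggered.

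A third inference is that people join after their commune's sequence is known, with identification bias and visits out of step with the commune. The documents do not say so. "After baseline assessment, communes will be randomly assigned to the three sequences" is the protective order, and the sequence is held by someone outside the study. Naturalistic entry can simply describe how people come forward. The article gives no closing date, but a full protocol may. Any example of a late entrant's visits falling in the wrong step would depend on Table 1 shading that is not visible in the text at hand.

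The reply does not remove the conflict over unit, groups and stop, or the use of 336 as an enrolment figure. The latter also appears in the sample size section, so it is more than loose wording in the abstract.

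**Conclusion.** The point holds as a contradiction to be corrected. The abstract's rule conflicts with commune randomisation after baseline to three sequences, and an enrolment stop at 336 conflicts with 8 recruited in each of 48 communes.

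If the stop were followed, about 294 would remain and power at 0.42 versus 0.30 would be about 76% (76 to 79% by choice of variance), against the stated 81%. This rests on the planned 12.5% attrition, a two-sided test and the stepped-wedge layout that reproduces Table 4.

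Loss of places in the last province is possible but conditional. At 8 per commune the stop falls after 7 of 8 districts under strictly sequential entry, and the effect is smaller with overlap. The documents do not show that the trial is individually randomised, that a province will be lost, or that enrolment stays open after allocation is known.

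**What to change.** - Replace the abstract sentence with the body's rule: communes are randomised after baseline assessment to three sequences, 1:1:1, stratified by district.
- In the abstract and the sample size section, give 384 as the enrolment target and 336 as the number expected after attrition.
- Set recruitment per commune across all 48, at an average of 8 with a tolerance that keeps that average, and no trial-wide stop at 336. A hard ceiling of 8 should be avoided: slow communes could not be offset, and the average would fall below plan.
- Confirm that each district's trial enrolment closes before its commune sequences are released, in keeping with randomisation after baseline.

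**Cost.** Mostly wording. Fast communes may have to turn away late volunteers. Enrolment is 384 − 336 = 48 higher than a stop at 336 implies, but 8 per commune already plans for these. If 336 is to stay as the enrolled number, the stated power should be restated as about 76%.

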## Introduction

### Background and rationale

Mental disorders account for 13% of the global burden of disease [1]. Global prevalence rates for depression and anxiety disorders, the two most common mental disorders [2], are estimated at 4.4% and 3.6%, respectively [3], with anxiety frequently co-occurring with depression [4]. Despite this, there is an overwhelming gap in mental health treatment, especially in low- and middle-income countries (LMICs) [5], which bear 80% of mental disorders disease burden [6]. A major contributor to the treatment gap is a shortage of health human resources (e.g., psychiatrist, psychiatric nurses) [7]. In Vietnam, an LMIC, the treatment gap for depression is 83% [8]. The very limited human resources for mental health are generally available only in tertiary-care facilities in large urban centres [9], where depression care is focused predominantly on pharmacological treatment in the critical absence of counseling and psychosocial interventions [9]. Epidemiological evidence suggests that depression prevalence in Vietnam is similar to global rates [10,11]. Most of the estimated four million persons living with depression in Vietnam, particularly those living in the country’s rural and remote areas, have very limited access to treatment, care and support.

The COVID-19 pandemic has had a profound impact on population mental health, with certain populations, such as those residing in rural and remote areas with limited access to resources, disproportionately affected [12]. The pandemic has also amplified existing gaps and inequities in mental health care [13–15], leading to an increased urgency to expand crucial evidence-based and low-barrier mental health care. The severe and persistent shortage of human resources for mental health is a continuing impediment to meeting population mental health service needs. The necessary shift to remote care delivery during the COVID-19 pandemic lockdowns has highlighted the promise of digital health interventions, including smartphone apps, as a feasible means to scaling up access to mental health services [16,17]. In response there has been an explosion of smartphone apps for common forms of mental illnesses, including depression and anxiety, as many countries recognize the opportunity for harnessing the capabilities of digital technologies globally. Current evidence for these interventions, however, is limited [17–19].

The annual economic costs directly attributable to mental illnesses is estimated at USD $1.15 trillion globally [8]. The returns on investment for scaling-up the response to the massive public health and economic burden of depression, therefore, have been suggested to be substantial, with an estimated benefit to cost ratio of 5.7 in LMICs when the value of health and economic benefits is considered [8]. A recent systematic review on economic evaluations of digital health interventions for depression has provided promising evidence for the cost-effectiveness of such interventions [20]. However, all studies included in the review were from high-income countries, further underlining the large gap in the evidence-base on the cost-effectiveness of interventions for depression in LMICs [21].

The objective of this trial is to test the effectiveness and cost-effectiveness of a digital mental health intervention called VMood in Vietnam. VMood is a smartphone-based depression intervention adapted from an in-person Supported Self-Management (SSM) intervention developed in Canada. SSM is a low-cost approach where providers support people to recover from depression [22]. It is grounded in principles of Cognitive Behavioural Therapy and utilizes an *Antidepressant Skills Workbook* (ASW) and a task-sharing approach, wherein non-specialist providers (e.g., lay health worker, community health worker) are trained to provide coaching support to individuals working through the ASW [22]. Task-sharing has emerged as a key strategy for scaling up mental health services, especially in low-resource contexts [2,23,24].

From 2016–2019, we conducted a trial to test the effectiveness of the in-person SSM intervention in community-based settings across eight provinces in Vietnam [25]. Non-specialist providers, supervised by primary care providers, delivered support to 376 adults with depression caseness (defined as score of ≥8 on the Self-Reporting Questionnaire [SRQ-9]) across 8 provinces in Vietnam. Two districts and two communes (municipal subdivisions) were randomly selected from each province, for a total of 16 districts and 32 communes. Randomization occurred at the commune level. The primary outcome was the effect of the SSM intervention on change in depression scores, and the primary analysis was intention-to-treat. Results showed that receiving the SSM intervention reduced the odds of having depression by 58% compared with the control group, who received care as usual, demonstrating that accessible treatment by non-specialists in community settings is effective for mild to moderate depression [25].

In Vietnam, the Ministry of Labour, Invalids, and Social Affairs (MOLISA) and Ministry of Health (MOH) are jointly responsible for managing mental health services, with MOH responsible for the national psychiatric hospitals and MOLISA responsible for the Social Protection Centres that provide rehabilitation and social support services [26]. Over the past two and a half decades, the Government of Vietnam has focused increasing attention on strengthening its mental health system, implementing national programs of reform aimed at improving population mental health [26], culminating in the recent national program on Social Assistance and Functional Recovery for People with Disabilities, Autistic Children, and People with Mental Disorders in the 2021–2030 period, a commitment to community-based programs and information technology for mental health promotion and management [27]. This is in recognition of the key role digital health interventions can play in the context of severely constrained resources for mental health that are likely to persist [28] and the pressing need for virtual care amidst and beyond the COVID-19 pandemic.

In response, we adapted the in-person SSM intervention to a digital intervention (*VMood*), to be delivered via a smartphone app. VMood consists of three-months’ engagement with the VMood program components, adapted from the ASW, and online coaching support delivered by a MOLISA social worker virtually through the app. This paper describes the trial protocol for this study that will assess the effectiveness of the VMood intervention, beginning with feasibility testing. Alongside the trial a cost-effectiveness analysis will be conducted to capture the costs and benefits of the intervention. With ongoing support from the Government of Vietnam, we will implement VMood across eight provinces in Vietnam.

